#### Run-In Period

We will randomize after the completion of a 7-day run-in period. Estimates of mindfulness and meditation app user retention over 28 days indicate that most attrition (approximately 90%) occurs within the first 7 days of app installation [21]. Therefore, the run-in period will be used to select the participants most likely to complete study measures. During the run-in period, we will ask participants to complete daily measures (refer to the Outcomes section) as well as listen to four short (5 min) “preparation for meditation” audios covering the following topics: (1) background of the teacher and mindfulness, (2) introduction to the concept of mindfulness, (3) introduction to mindfulness practice, and (4) results from practicing mindfulness. All this content will be accessed via a series of Qualtrics surveys (Qualtrics International Inc) that will be emailed to participants daily. Participants will also be asked to respond to measures that cover personality, sleep, and motivations and expectations. Participants will have successfully completed the run-in period if they engage with ≥57% (ie, at least 4 of the 7 days) of the run-in content.

We will monitor participant response patterns during the run-in period. If such monitoring raises suspicions about the accuracy of the information provided in the prescreening survey (ie, related to the eligibility criteria—most notably, participant identity and country of residence), additional verification procedures may be required. Participants flagged as suspicious who fail to complete or successfully pass additional verification procedures (refer to the Eligibility Criteria section) will be excluded from the study.

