#### Intervention Period

Participants who successfully complete the run-in period will be first asked to complete outcome measures at T0 (baseline) via Qualtrics. After completing outcome measures, participants will be randomized to 1 of the 4 study groups and provided with a unique participant identification code along with instructions on how to access the intervention materials. Participants will be asked to use only the specific mindfulness instructions provided for 28 days and complete all survey items when prompted. Throughout the 28-day period and at the conclusion of the intervention, participants will be prompted to complete outcome measures as specified in the Outcomes section.

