### Outcomes

#### Overview

*Personality* will be measured on days 2 and 3 of the run-in period using the short form of the Big Five Inventory, a 30-item measure of personality across 5 domains: open-mindedness, conscientiousness, extraversion, agreeableness, and negative emotionality [32].

*Sleep* will be assessed on day 4 of the run-in period using a single item from the Sleep Quality Scale [33]: “During the past week, how would you rate your sleep quality overall?” (response options: *terrible*=1, *poor*=2-4, *fair*=5-7, *good*=7-9, and *excellent*=10).

*Motivations and expectancy* will be measured on day 4 of the run-in period using the following questions: (1) “How much benefit do you expect from this mindfulness meditation course?” (response options: not at all to very much), (2) “What is your main goal for completing this mindfulness meditation course?” (goal or motivation free-text field), (3) “How motivated are you by this goal?” (response options: not at all to very much), (4) “How much improvement or progress toward your goal do you expect from the course?” (response options: none at all to a great deal), and (5) “How confident are you that the amount of improvement or progress you indicated will occur?” (response options: not confident at all to extremely confident).

The outcome measures in the following paragraphs will be obtained at baseline (T0) and the midintervention (T0.5) and postintervention (T1) time points and after a 1-month follow-up period (T2) unless otherwise indicated.

*Psychological well-being (primary outcome)* will be assessed at T0, T1, and T2 using the Warwick-Edinburgh Mental Wellbeing Scale (WEMWBS) [34], which includes 14 positively worded items of mental well-being for the previous 2 weeks on a 5-point Likert scale from 1 (none of the time) to 5 (all of the time). The primary outcome measurement is at T1. Previous analyses of responsiveness to change analyses indicate that the WEMWBS detects individually meaningful improvement across a variety of mental health measures [35]. These analyses indicated an average SE of measurement over time of 2.69.

*Psychological distress (secondary outcome)* will be assessed at T0, T0.5, T1, and T2 using the Kessler Psychological Distress Scale [36], a 10-item self-report measure of psychological distress over the previous month, on a 5-point Likert scale from 1 (none of the time) to 5 (all of the time).

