### Sample Size

A meta-analysis of meditation apps [1] indicates a standardized mean difference (SMD) effect size of 0.29 (95% CI 0.14-0.45) for psychological well-being when comparing apps to controls. A more recent study [6] randomized participants to approximately 10 or 30 minutes of sitting or movement practice for 2 weeks. They estimated a difference in the effects on the WEMWBS between the sitting groups of short and long duration of SMD=0.2 to 0.25. To be conservative, we determined a target sample size with an SMD of 0.2.

On the basis of an SD in WEMWBS scores of 9.84 [55] and a within-individual correlation of 0.83 in repeated assessments of the WEMWBS [34], we would need a final sample size of 688 participants to achieve 80% power (at the 2-sided *P*=.02 significance level to correct for multiple comparisons between conditions) to detect a difference of 1.97 points (SMD=0.2) for each active condition (10, 20, and 30 min) compared to one another and with the minimal-dose condition. This would translate to approximately 172 participants per arm. These calculations were conducted using the *sampsi* package in Stata (StataCorp).

Meditation app studies indicate overall retention rates of approximately 60% for active mindfulness meditation interventions [1]. Given our use of a run-in period, the aim of which is to allow participants who are most likely to disengage to do so before randomization, we anticipate postrandomization retention rates approximating 80%. In total, we will then recruit on a rolling basis until we achieve the required sample size at randomization of 860.

We will aim to recruit the full sample by March 31, 2025. We will conduct an interim analysis at this stage if the sample is at <90% of the target. If the sample is at ≥90% of the target by March 31, 2025, recruitment will be terminated. If continued recruitment is necessary (ie, we recruit <90% of the sample by March 31, 2025), recruitment will continue until the target sample is reached or 6 months (from March 31, 2025) have elapsed (whichever occurs first). If an interim analysis is required, the team member who undertakes this analysis will not implement the final analysis (as they will need to be unblinded). Other members of the team will undertake the final analysis and will alter the arm designation in the analytic code to further blind results relative to the interim analysis.

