#### Effectiveness Analyses

A constrained longitudinal data analysis method [57] will be used to build the linear mixed-effects model estimating the effect of the interventions on the primary outcome. The model will incorporate study visit (T0 and T1) as a categorical variable, intervention (10, 20, and 30 min each vs the minimal dose), and intervention by study visit interaction as main effects. The model will assume a common baseline mean of the outcome across the 4 intervention groups and an unstructured variance-covariance among the repeated measurements.

Models analyzing secondary outcomes will incorporate study visit (T0, T0.5, and T1) and intervention (10, 20, and 30 min each vs the minimal dose) as categorical variables. Secondary continuous outcomes will be analyzed similarly to the primary outcome (ie, the constrained longitudinal data analysis described previously). Additional analyses will include follow-up assessments (ie, T2) in the model.

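### The primary model adjusts only for one T0 WEMWBS score, although other T0 scores are already in hand and a week of run-in surveys comes first: a modest, optional precision gain is left unused

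*Protocol article*

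**What the plan says.** The Outcomes overview schedules the primary outcome at three visits: it "will be assessed at T0, T1, and T2 using the Warwick-Edinburgh Mental Wellbeing Scale (WEMWBS"). T0 is taken once, after the run-in and before allocation (Intervention Period): "Participants who successfully complete the run-in period will be first asked to complete outcome measures at T0 (baseline) via Qualtrics".

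Before that comes a week of survey contact (Run-In Period): "We will randomize after the completion of a 7-day run-in period". The surveys go out by email every day of that week, and the section names what they measure beyond the audio content: "Participants will also be asked to respond to measures that cover personality, sleep, and motivations and expectations". Prescreening Measures and the Outcomes overview place supplementary sociodemographics on day 1, personality on days 2 and 3, and sleep and expectancy on day 4. No run-in or prescreening text names the WEMWBS. The timeline figure is not available, so this rests on the text.

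The K10 and the PROMIS Anxiety and Depression short forms are secondary outcomes and are also collected at T0.

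For the primary analysis (Effectiveness Analyses): "The model will incorporate study visit (T0 and T1) as a categorical variable". The other terms are intervention and its interaction with visit, with a common baseline mean and unstructured covariance. No covariate is listed. The Sample Size section assumes "a within-individual correlation of 0.83 in repeated assessments of the WEMWBS".

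The abstract adds a midintervention WEMWBS that the Outcomes section does not have. That visit follows randomization and does not affect this point.

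**The concern.** The trial looks for a small difference, 1.97 points (SMD 0.2), at a strict level. With a T0–T1 correlation of 0.83, one T0 score leaves 1 − 0.83² = 31% of the T1 variance unexplained. Part of that remainder may be predictable from other prerandomization data.

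Two sources are at hand. The T0 distress, anxiety and depression scores precede allocation but are not in the primary model. The run-in collects a 30-item personality inventory but not the 14 items of the primary outcome; a second score would average out some of the occasion-to-occasion noise in T0. Because everything involved precedes allocation, its use cannot depend on assigned dose. What is at stake is precision, not validity.

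**Working it through.** **Inputs from the protocol.** Sample Size: SD 9.84, correlation 0.83, difference 1.97, two-sided .02, 172 per arm (688 analysed). Outcomes overview: SE of measurement 2.69, recall window 2 weeks.

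**Reproducing 688.** For a change score the variance factor is 2(1 − 0.83) = 0.34. Then n = 2 × (2.326 + 0.842)² × 9.84² × 0.34 / 1.97² ≈ 170.3, so 171 per arm and 684 in total. This matches 172 and 688 closely.

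**The planned model.** A constrained longitudinal model behaves about like ANCOVA, with factor f = 1 − 0.83² = 0.3111.
- SE = √(2 × 9.84² × 0.3111 / 172) = 0.592.
- Power = Φ(1.97/0.592 − 2.326) ≈ 84%.

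The sample size was thus computed for a slightly less efficient analysis than the one planned.

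**Adding the T0 covariates.** The documents give no partial R-squared, so a range of 0.02 to 0.10 is assumed. The factor becomes 0.3111 × (1 − R²).

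| Assumed partial R² | Factor | SE | Power |
|---|---|---|---|
| 0.02 | 0.305 | 0.586 | 85% |
| 0.05 | 0.296 | 0.577 | 86% |
| 0.10 | 0.280 | 0.561 | 88% |

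**Adding a run-in WEMWBS.** Let r₂ be its correlation with T1 and r_b its correlation with T0. Then f₂ = 1 − [0.83² + r₂² − 2 × 0.83 × r₂ × r_b] / (1 − r_b²). Neither r₂ nor r_b is given. The stated SE of measurement implies a reliability of 1 − (2.69/9.84)² = 0.925, used as r_b in two rows.

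| r_b | r₂ | f₂ | Variance cut | Power at 172 per arm |
|---|---|---|---|---|
| 0.90 | 0.83 | 0.275 | 11.7% | 89% |
| 0.90 | 0.80 | 0.296 | 4.8% | 86% |
| 0.925 | 0.83 | 0.284 | 8.6% | 88% |
| 0.925 | 0.80 | 0.304 | 2.3% | 85% |
| 0.95 | 0.83 | 0.293 | 5.7% | 86% |
| 0.95 | 0.80 | 0.310 | 0.4% | 84% |

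These figures assume that everyone has the score. If a share s has it, the pooled factor is roughly 1 / [(1 − s)/0.3111 + s/f₂]. Taking the two rows at r_b = 0.90, s = 25% gives a cut of about 1 to 3% and s = 50% about 2 to 6%.

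**The case against.** The strongest reply is that nothing is wrong. One baseline score in a constrained longitudinal model is standard and efficient, and it already exceeds the 80% target. That stands, and it is why this is only a suggestion. One qualification: the 84% holds at .02. The plan states comparisons among all four arms, which is six contrasts; at .05/6 = .0083 the same model has about 75.5% power, so spare precision may still be useful.

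A second reply is that covariate lists commonly belong in the analysis plan, which is not shown. That is fair: if the analysis plan already lists these covariates, the main part of the point falls away. The Sensitivity Analysis section's provision for variables related to missingness serves a different purpose. Prescreening also excludes severe K10 and PROMIS scores, which restricts their range and may put the gain near the low end.

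A reader might apply 0.83 to every pair of scores and infer a 21% variance reduction and 92% power from a run-in score (f₂ = 0.247). The documents do not support that as a headline. It requires scores about a week apart, with overlapping recall windows, to correlate no better than scores four weeks apart. It also conflicts with the stated SE of measurement: if the true score is stable before randomization, even unlimited prerandomization scores would leave 1 − 0.83²/0.925 = 0.255, a cut of about 18%. That bound is indicative only, because the SD and SE of measurement come from different sources. Nor is 5% a floor; the table shows 0.4%.

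Timing limits the run-in option further. Enrolment began in 2024, the protocol records a screening change dated March 12, 2025, and recruitment was to end on March 31, 2025, or at most six months later. Participants already past the run-in gain nothing.

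**Conclusion.** The point holds as a modest missed efficiency, with low priority. As described, the primary model draws on one T0 WEMWBS and no other prerandomization information, although useful scores are already collected.

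Using the T0 covariates would raise power from about 84% to about 85–88%, conditional on the assumed partial R-squared of 0.02 to 0.10. A run-in WEMWBS would cut the variance by near 0 to about 12% among those who have it (about 9% with the stated SE of measurement and no decay over time), conditional on correlations that the documents do not give. The gain shrinks roughly in proportion to the share of the sample that has the score.

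A reader should not conclude that the sample size is wrong or the trial underpowered for this reason: 688 reproduces, and the planned analysis does slightly better than the calculation behind it.

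**What to change.** **Main change, no new data.** Before unblinding, prespecify T0 K10, PROMIS Anxiety and PROMIS Depression, each by visit, as covariates in the primary constrained longitudinal model. The cost is wording in the analysis plan. All three are requested before allocation, so missing values should be few.

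**Optional, for participants still to enter the run-in.** Add the 14-item WEMWBS to an early run-in survey, for example day 1 with the sociodemographic questions. Model it as a second prerandomization occasion with a common mean across arms and unstructured covariance. Participants without it stay in through the likelihood. The cost is a short amendment and an estimated 2–3 minutes on one run-in day. Some day-1 scores will be missing, because passing the run-in requires only 4 of 7 days, and those already enrolled gain nothing. If few participants remain to be recruited, only the first change is worth making.

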#### Weekly Measures

During the intervention period, additional measures will be obtained weekly (ie, 7, 14, 21, and 28 days after the baseline survey).

*Mindfulness* practice will be assessed using the following items: (1) “In the past week, how many daily sessions of this study’s meditation program did you complete?” (response options: 0-7); (2) “In the past week, on the days you meditated with the study program, approximately how many minutes (on average) was each meditation session?”; (3) “In the past week, how many additional days did you practice meditation?” (response options: 0-7) and “In the past week, on the days you meditated in addition to the study program, approximately how many minutes (on average) was each meditation session?”; (4) “On the days you practised meditation, how many minutes per session did you practice? (this includes the guided sessions in the meditation program)” (response options: 0 to ≥60 min); and (5) “In the past week, how often did you engage in informal mindfulness practice? i.e. mindfully washing dishes, showering, walking etc.” (response options: none of the time to all of the time).

*Adverse events* will be assessed using a modified short form of the Meditation-Related Adverse Effects Scale [50].

*Sleep* will be assessed using a single item from the Sleep Quality Scale [33]: “During the past week, how would you rate your sleep quality overall?” (response options: *terrible*=1, *poor*=2-4, *fair*=5-7, good=7-9, and *excellent*=10).

*Expectancy* will be assessed using the following item: “How effective do you think your training so far has been for your [goal or motivation free-text field from run-in survey]?” (response options: not at all effective to very effective).

#### Momentary Measures

Participants will be assessed on study variables *daily*, before and after each meditation practice session. Meditators will respond to questionnaires assessing momentary mood before and after each meditation. Following the postmeditation mood items, meditators will complete 1 random questionnaire from a list of questionnaires assessing state mindfulness, decentering, mindful attitudes (including nonjudgment, nonattachment, and curiosity), and attention (attention regulation and self-regulation).

Participants who choose to skip a meditation session will be queried about their momentary mood and assessed on 1 random questionnaire from a list of questionnaires assessing disposition mindfulness, decentering, and attention control variables in the previous 24 hours.

*Momentary mood* will be assessed daily, before and after each meditation session, using a modified English version of the Multidimensional Mood Questionnaire [51]. The Multidimensional Mood Questionnaire assesses valence, arousal, and calmness dimensions of momentary mood using 6 items on a 7-point Likert scale (with the end points labeled as “very”). Participants will respond to the following statement—“At this moment I feel:”—with the following options: (1) tired-awake, (2) content-discontent, (3) agitated-calm, (4) energetic–lacking energy, (5) well-unwell, and (6) relaxed-tense.

*State mindfulness* will be assessed using a brief 6-item version of the State Mindfulness Scale [52]. The chosen items are among the highest-loading items on the original scale. Participants will respond to the following statement—“Please use the rating scale to indicate how well each statement describes your experience during the meditation:”—on a 5-point Likert scale with options ranging from 1 (not at all) to 5 (very well).

*Attention* will be assessed using the attention regulation and self-regulation subscales of the Multidimensional Assessment of Interoceptive Awareness [53] scale. A selection of 9 items based on the highest-loading items on the original subscales will be used to capture attention within the meditation session [53]. Participants will respond to the following statement—“Please indicate how often each statement applied to you during the meditation:”—on a 6-point Likert scale ranging from 1 (*never*) to 6 (*always*).

*Decentering* will be assessed using a brief 5-item version of the decentering subscale of the Toronto Mindfulness Scale [54]. The chosen items are among the highest-loading items on the original subscale. Participants will respond to the following statement—“Please indicate the extent to which each statement describes what you just experienced during the meditation:”—on a 6-point Likert scale ranging from 1 (not at all) to 6 (very much).

*Mindful attitudes* will be assessed using a face-valid selection of (1) Toronto Mindfulness Scale items to reflect attitudes of nonjudgment (acceptance or allowance) and curiosity [54], (2) Five Facet Mindfulness Questionnaire nonjudgment subscale items to reflect nonjudgment (nonevaluative aspect), and (3) Nonattachment Scale items to reflect nonattachment. Participants will respond to the following statement—“Please indicate the extent to which you agree each statement describes what you just experienced during the meditation:”—using a 5-point Likert scale ranging from 1 (not at all) to 5 (very much).

### Participant Timeline

A timeline of all major study milestones is provided in Figure 2. For brevity, daily and weekly survey items have been excluded.

**Figure 2 figure2:**
[figure not shown]
Study timeline. Momentary measures collected daily between T0 and T1 are excluded. T0, T0.5, T1, and T2 represent time points before randomization, midintervention (2 weeks after randomization), postintervention (4 weeks after randomization), and follow-up (8 weeks after randomization). ATTC-SF: Attention Control Scale–Short Form; DASS-21: Depression, Anxiety, and Stress Scale; DERS-SF: Difficulties in Emotion Regulation Scale–Short Form; EQ: Experiences Questionnaire; EQUA-S: Two-Factor Equanimity Scale; FFMQ: Five Facet Mindfulness Questionnaire; K10: Kessler Psychological Distress Scale; MRAE: Meditation-Related Adverse Effects Scale; NAS-7: Nonattachment Scale; PERS-S: Perth Emotional Reactivity Scale–Short Form; PROMIS: Patient-Reported Outcomes Measurement Information System; RNTQ: Repetitive Negative Thoughts Questionnaire; SAD-D: Social Anxiety Disorder Severity Scale; SQS: Sleep Quality Scale; WEMWBS: Warwick-Edinburgh Mental Wellbeing Scale.

### Sample Size

A meta-analysis of meditation apps [1] indicates a standardized mean difference (SMD) effect size of 0.29 (95% CI 0.14-0.45) for psychological well-being when comparing apps to controls. A more recent study [6] randomized participants to approximately 10 or 30 minutes of sitting or movement practice for 2 weeks. They estimated a difference in the effects on the WEMWBS between the sitting groups of short and long duration of SMD=0.2 to 0.25. To be conservative, we determined a target sample size with an SMD of 0.2.

On the basis of an SD in WEMWBS scores of 9.84 [55] and a within-individual correlation of 0.83 in repeated assessments of the WEMWBS [34], we would need a final sample size of 688 participants to achieve 80% power (at the 2-sided *P*=.02 significance level to correct for multiple comparisons between conditions) to detect a difference of 1.97 points (SMD=0.2) for each active condition (10, 20, and 30 min) compared to one another and with the minimal-dose condition. This would translate to approximately 172 participants per arm. These calculations were conducted using the *sampsi* package in Stata (StataCorp).

Meditation app studies indicate overall retention rates of approximately 60% for active mindfulness meditation interventions [1]. Given our use of a run-in period, the aim of which is to allow participants who are most likely to disengage to do so before randomization, we anticipate postrandomization retention rates approximating 80%. In total, we will then recruit on a rolling basis until we achieve the required sample size at randomization of 860.

We will aim to recruit the full sample by March 31, 2025. We will conduct an interim analysis at this stage if the sample is at <90% of the target. If the sample is at ≥90% of the target by March 31, 2025, recruitment will be terminated. If continued recruitment is necessary (ie, we recruit <90% of the sample by March 31, 2025), recruitment will continue until the target sample is reached or 6 months (from March 31, 2025) have elapsed (whichever occurs first). If an interim analysis is required, the team member who undertakes this analysis will not implement the final analysis (as they will need to be unblinded). Other members of the team will undertake the final analysis and will alter the arm designation in the analytic code to further blind results relative to the interim analysis.

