### Statistical Methods

#### General Principles

The primary analysis will be undertaken on the primary outcome following the intention-to-treat approach [56]. The intention-to-treat analysis sample will consist of all randomized participants, assigning them to the arms they were randomized to independently of their subsequent behavior. An intention-to-treat approach was chosen for the primary analysis because the study’s main purpose is to test whether larger *prescribed* doses of mindfulness practice yield larger effects on well-being. Intention-to-treat analyses will also be conducted for all secondary outcomes. Additional secondary analyses will be conducted following the per-protocol approach for all outcome measures (ie, primary and secondary). For data collected at weekly increments between T0 and T1, measurement occasions will be nested within individual participants.

The comparisons of interest will be each intervention (10, 20, and 30 min) compared to one another and with the minimal dose for each outcome (mean difference and 95% CI).

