#### Multiple Testing Adjustment

For the analysis of the primary outcome, we will use a Bonferroni adjustment to control the type I error rate for the primary outcome across all 3 pairwise comparisons by setting the 2-sided significance level at .02. For analyses of secondary outcomes, with nominal α set at *P*<.05, we will adjust for multiple comparisons at the variable level using the false discovery rate procedure [64], which is less conservative than the Bonferroni correction and, therefore, may provide a better balance than Bonferroni between the likelihood of type 1 and type 2 errors.

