### Strengths and Limitations

When compared to previous empirical dose-response assessments, our study has several notable strengths and some limitations. These are described in the following paragraphs.

Our study has several characteristics that will improve our capacity to make inferences about dose-response effects for mindfulness practices compared to previous studies that have tested dose-response effects for mindfulness meditation. Our targeted sample size (N≥866) is powered to detect small effects (*d*=0.2 approximately) between active dose conditions. The program length is 28 days, which will allow us to test for changes in more stable “trait” effects. There is considerable variation in doses for daily sessions, ranging from 10 to 30 minutes. These doses are based on a nonsystematic search of the literature, MBPs, and mindfulness apps with dosage recommendations (for details, refer to the study by Bowles et al [11]). The random allocation of participants to different doses will allow us to make inferences about the effects of different doses, which are less subject to bias than those in previous assessments [3,10]. Finally, while our primary outcome is well-being, we have a range of outcome measures covering different aspects of well-being and mental health, as well as hypothesized mechanisms of change for mindfulness interventions, including decentering and emotional reactivity.

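### The 80% power at SMD 0.2 is correct as a conditional figure, but the cited 10 versus 30 minute effect does not support 0.2 for both adjacent steps, and the weaker step has at most about 23-40% power

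*Protocol article*

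**What the plan says.** The Sample Size section cites two effects. One is an SMD of 0.29 (95% CI 0.14-0.45) for meditation apps against controls. The other comes from a 2-week randomised study of roughly 10 or 30 minutes of practice: "They estimated a difference in the effects on the WEMWBS between the sitting groups of short and long duration of SMD=0.2 to 0.25". The section then says: "To be conservative, we determined a target sample size with an SMD of 0.2".

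From an SD of 9.84 and a within-person correlation of 0.83 it concludes that "we would need a final sample size of 688 participants to achieve 80% power" at two-sided .02 "to detect a difference of 1.97 points (SMD=0.2) for each active condition (10, 20, and 30 min) compared to one another and with the minimal-dose" arm. It adds: "This would translate to approximately 172 participants per arm".

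General Principles makes every pair a target of inference: "The comparisons of interest will be each intervention (10, 20, and 30 min) compared to one another and with the minimal dose for each outcome". Strengths and Limitations presents the power as an advantage over earlier studies, saying that the sample "is powered to detect small effects (*d*=0.2 approximately) between active dose conditions". No separate effect is given for 10 v 20 or for 20 v 30 minutes.

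**The concern.** An effect observed across the full active range, 10 to 30 minutes, is applied unchanged to each half of that range. For 10 v 30, taking the lower end of 0.2 to 0.25 is a cautious choice. For both 10 v 20 and 20 v 30 it is not, because two steps of 0.2 would imply a 10 v 30 difference of 0.4, which is 1.6 to 2 times the cited figure.

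The adjacent comparisons bear directly on the trial's question of whether a longer daily practice does more than a shorter one. Under the plan's own first hypothesis and its own cited effect, at least one of the two would more often than not be non-significant. With an 80% figure on record for every pair, a reader could take that result as evidence of a plateau when it is what the design would usually produce even if the dose-response were real.

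**Working it through.** **Inputs (all from the protocol).** SD 9.84, r = 0.83, difference 1.97 points, 80% power, 172 per arm, and 10 v 30 effect SMD 0.2 to 0.25 (Sample Size); alpha .02 two-sided (Sample Size and Multiple Testing Adjustment); linear and log-linear dose shapes (Additional Analyses). Normal quantiles: z(.99) = 2.326 and z(.80) = 0.842, so (2.326 + 0.842)² = 10.036.

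**1. Reproduce the stated N.** With change-score variance factor 2(1 − 0.83) = 0.34:

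n per arm = 2 × 10.036 × 0.34 × (9.84/1.97)² = 170.3, so 171 per arm and 684 in total, against 172 and 688 stated. Power at 172 per arm is 80.4%.

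With the baseline-adjusted factor 1 − 0.83² = 0.3111, which is closer to the planned constrained longitudinal model, n = 155.8 per arm (156), and power at 172 is 84.2%. Both factors are carried below.

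**2. Bound on the adjacent steps.** On a common SD, d(10,30) = d(10,20) + d(20,30). If neither step is negative, the smaller is at most half the total: 0.10 when d(10,30) = 0.20, and 0.125 when it is 0.25. No linearity is assumed.

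**3. Power of the weaker step at 172 per arm.** Power = P(Z > 2.326 − d/SE), with SE = √(2 × factor/172), which is 0.0629 (change score) or 0.0601 (baseline-adjusted).

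- d = 0.10: d/SE = 1.590 or 1.663, power 23% or 25%.
- d = 0.125: d/SE = 1.988 or 2.078, power 37% or 40%.

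These are upper limits, reached only when the two steps are equal.

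**4. All pairs under the two shapes the protocol names, scaled to the cited 10 v 30 effect.** Linear: d(a,b) = d(10,30) × (b − a)/20. Log-linear: d(a,b) = d(10,30) × ln(b/a)/ln 3. Each cell gives the SMD, then power in % (change score / baseline-adjusted).

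| Pair | Linear, 0.20 | Log-linear, 0.20 | Linear, 0.25 | Log-linear, 0.25 |
|---|---|---|---|---|
| 10 v 20 | 0.100: 23/25 | 0.126: 37/41 | 0.125: 37/40 | 0.158: 57/62 |
| 20 v 30 | 0.100: 23/25 | 0.074: 12/14 | 0.125: 37/40 | 0.092: 20/21 |
| 10 v 30 | 0.200: 80/84 | 0.200: 80/84 | 0.250: 95/97 | 0.250: 95/97 |
| 4 v 10 | 0.060: 9/9 | 0.167: 63/67 | 0.075: 13/14 | 0.209: 84/87 |
| 4 v 20 | 0.160: 59/63 | 0.293: 99/99 | 0.200: 80/84 | 0.366: >99 |
| 4 v 30 | 0.260: 96/98 | 0.367: >99 | 0.325: >99 | 0.459: >99 |

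The rows with 4 minutes extrapolate below the cited study's range and are illustrative only.

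**5. Scale of the gap.** For 80% power at SMD 0.10, n = 2 × 10.036 × 0.34/0.01 = 683 per arm (change score), or 2 × 10.036 × 0.3111/0.01 = 625 per arm (baseline-adjusted), against 172.

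**The case against.** The strongest reply is that a power statement is conditional. The section promises 80% power to detect 1.97 points and does not say that each pair is expected to differ by that much. This stands as arithmetic, and a reader who inferred that 688 is miscalculated would be wrong. It does not rescue the justification. The protocol does not present 0.2 as a smallest important difference; it derives 0.2 from cited effects and calls it conservative, and that reasoning does not carry over to both half-range contrasts.

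A reader might also infer that the 80% holds for 10 v 30 alone. The documents do not support that. Under the first hypothesis, 30 v 4 is at least as large as 30 v 10, and its power is 96% or more in every scenario above. The 20 v 4 contrast reaches 80% in three of the four. The cited 0.29 also has some bearing on active versus minimal dose, although its controls are not described as a 4-minute meditation and it says nothing about gaps between active doses.

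The cited study ran 2 weeks and this programme runs 28 days, so a larger 10 v 30 effect is possible. The protocol gives no figure for one, and it would have to reach 0.4.

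Finally, General Principles already promises mean differences with 95% CIs. Additional Analyses plans linear and log-linear tests if any difference is seen, and the Introduction itself warns against treating missing evidence of a dose effect as proof that there is none. So dose-response does not rest on adjacent pairs alone, and nothing says a null adjacent result would be called a plateau. This lowers the stakes but leaves the power statement uncorrected.

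**Conclusion.** The concern holds in a limited form. The 688 is right for any single pair that truly differs by SMD 0.2. What fails is 0.2 as a conservative, evidence-based effect for both 10 v 20 and 20 v 30. If 10 v 30 is 0.20, the weaker adjacent pair has at most about 23-25% power; if 0.25, at most about 37-40%. These ceilings should not be read as the power of every adjacent comparison: on a log-linear curve 10 v 20 has 37-62% and 20 v 30 has 12-21%.

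The bound assumes additive mean differences on a common SD, an effect that does not fall between 10 and 30 minutes, the cited 0.2 to 0.25 as the 10 v 30 effect, and the plan's own SD, correlation, alpha and 172 analysed per arm. It should be corrected because the power claim is repeated as a strength of the trial, but it does not threaten the design.

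**What to change.** In Sample Size and in Strengths and Limitations:

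- State that the 80% is conditional on a true difference of 0.2 in the pair concerned. Say that the cited evidence supports this size for 30 v 10 and, under the first hypothesis, for 30 v 4, and that 0.2 is not conservative for 10 v 20 and 20 v 30.
- Give the power for 10 v 20 and 20 v 30 under linear and log-linear curves scaled to a 10 v 30 effect of 0.2 to 0.25. Give 10 v 4 and 20 v 4 alongside, labelled as illustrative extrapolations.
- State that a non-significant adjacent contrast will be interpreted from its confidence interval and not as a plateau or as equivalence of the two doses.

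No change is needed to the sample size, outcome, tests or models. The cost is a wording amendment and a less favourable stated power for adjacent doses.
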